## Abstract

**Background:**

The increasing prevalence of diabetes is placing important demands on the Chinese health care system. Providing self-management programs to the fast-growing number of people with diabetes presents an urgent need in rural primary care settings in China. Peer support has demonstrated effectiveness in improving self-management for individuals with diabetes in urban communities in China. A priority then becomes developing and evaluating a peer support program in primary care settings in rural communities of China and determining whether it is feasible and acceptable.

**Objective:**

The aims of this study are (1) to evaluate the feasibility and acceptability of a peer support approach to type 2 diabetes self-management in rural primary care settings; (2) to identify enabler and facilitator factors likely to influence the peer support implementation; (3) to provide primary data and evidence for developing a version of the program suitable for a randomized controlled trial in rural primary care settings.

**Methods:**

Three townships will be sampled from 3 different counties of Anhui province as the study setting. Participants will be recruited based on these counties’ local primary care health record system. The peer supporters will be recruited from among the participants. The peer support program will be led by peer supporters who have completed 12 hours of training. It will be guided by primary care providers. The program will include biweekly meetings over 3 months with varied peer support contacts between meetings to encourage the implementation of diabetes self-management. Mixed methods will be used for evaluation. Qualitative methods will be used to collect information from health care system professionals, individuals with diabetes, and peer supporters. Quantitative methods will be used to collect baseline data and data at the end of the 3-month intervention regarding psychosocial factors and self-management practices.

**Results:**

The results will include (1) quantitative baseline data that will characterize type 2 diabetes self-management practices of individuals with diabetes; (2) qualitative data that will identify enablers of and barriers to self-management practices for individuals with type 2 diabetes in rural communities; (3) both qualitative and quantitative evaluation data, after the 3-month intervention, to demonstrate the feasibility and acceptability of the peer support approach for individuals with type 2 diabetes.

**Conclusions:**

Our findings will inform the design of a tailored intervention program to improve self-management among individuals with type 2 diabetes in rural primary care settings. If we find that the peer support approach is feasible and acceptable, we will develop a larger randomized controlled trial to evaluate effectiveness in multiple rural settings in the province.

**International Registered Report Identifier (IRRID):**

PRR1-10.2196/47822

## Introduction

### Background

#### Challenges of the Diabetes Situation in China

Diabetes is a growing public health challenge. Diabetes mellitus (DM) imposes a huge economic burden on national health care systems worldwide, including in China. The prevalence of diabetes among adults in China has reached 11.6%, comprising about 114 million people and making China the country with the largest number of individuals with diabetes in the world [1]. The prevalence of diabetes in rural areas increased from 8.2% in 2008 to 10.3% in 2010. Although the prevalence is still lower than in urban areas, the growth rate is higher than in urban areas [2]. Furthermore, two-thirds of Chinese adults with diabetes have complications, and only 20.3% exhibit satisfactory glycemic control [3]. To improve noncommunicable disease prevention and control in diseases including diabetes, the National Basic Public Health Service Program (NBPHSP) was launched as part of China’s health care reform initiated in 2009. Subsidized by national and local government budgets, the NBPHSP is mainly implemented by community and township health service centers and health stations in urban areas and village clinics in rural areas [4]. Health management of patients with hypertension and diabetes is an integral and pivotal part of the NBPHSP. However, gaps still exist between guidance on modifiable risk factors and field implementation in primary health care settings. Patients with type 2 diabetes blood glucose and related risk behavior interventions have not been sufficiently studied in primary care settings [5]. Chronic illnesses are largely self-managed, with most of the care becoming the responsibility of patients and their families or others involved in the daily management of their illnesses.

#### Diabetes Self-Management

Early users of the term *self-management* included Thomas Creer et al [6] in a 1976 book on the rehabilitation of chronically ill children. Creer and colleagues said that “the term of self-management indicated that the patient was an active participant in treatment.” Since that time, the term has been widely used, mainly in referring to chronic disease patient education programs. Self-management has been defined as referring to “whether one is engaging in a health promoting activity such as exercise or is living with a chronic disease such as asthma, he or she is responsible for day-to-day management.” [7] Prominent approaches emphasize 3 sets of tasks: medical or behavior management, role management, and emotional management [8]. Additionally, 5 core self-management skills are commonly emphasized: problem-solving, decision-making, resource use, forming a patient–health care provider partnership, and taking action [9].

DM is a progressive and chronic condition lasting the remainder of the patient’s life. It is widely recognized that self-management is the cornerstone of DM care and has the potential to prevent relevant complications and improve quality of life [10]. Accordingly, the success of the treatment for DM depends on the ability of the individual to successfully sustain effective self-management behaviors that include taking prescribed medications, following diet and exercise regimens, self-monitoring blood glucose, and emotionally coping with the rigors of living with diabetes [8]. The goals of diabetes self-management are to optimize metabolic control, prevent acute and chronic complications, and optimize quality of life while keeping costs acceptable. The management of type 2 DM (T2DM) has traditionally been provided by health care professionals who focus on medication and lifestyle changes that can improve glycemic control.

A meta-analysis of self-management programs in diabetes by Norris and colleagues [11] found that diabetes self-management education provided by health care professionals is effective for improving clinical outcomes and quality of life, at least in the short term, but that these benefits sharply decline only a few months after the intervention ends. Therefore, while essential, education is generally not sufficient for most patients to maintain these behaviors over a lifetime of diabetes. To avoid such declines in benefits, evidence indicates that interventions should include elements of social support from families, engagement of multidisciplinary health care professionals, and support from others with diabetes. It is useful for the person with T2DM to recruit allies in supporting self-management who understand the condition, other people with diabetes who can share experiences and tips, or professionals who encourage a collaborative relationship in which they offer advice and the individual chooses how best to use it based on their knowledge of their own body and condition [12].

Studies show that without sustained support, many adults will not succeed in managing their condition well, leading to worse health outcomes including expensive hospitalizations and avoidable complications [13]. Among all these approaches to ongoing follow-up, peer support for diabetes self-management has been considered a promising strategy to achieve sound long-term outcomes for diabetes patients.

#### Peer Support for Diabetes Self-Management

Peer support has been formally defined as “the provision of emotional, appraisal, and informational assistance by a created social network member who possesses experiential knowledge of a specific behavioral stressor and similar characteristics as the target population, to address a health-related issue of a potentially or actually stressed focal person” [13]. Peer support may reduce feelings of isolation and loneliness, provide information about access to health services or the benefits of behaviors that positively improve health and well-being, and encourage more positive health practices [14]. Peer support programs have been widely recognized as promising for facilitating self-management behaviors among individuals with T2DM. Evidence demonstrates that the self-management practices of patients with diabetes are influenced by their knowledge, attitude, self-efficacy, and the presence of a supportive interpersonal, community, and policy environment [15]. The peer support approach emphasizes bringing a group of people with the same condition together to share their self-management challenges and address them as a group rather than using a professional leader who may focus purely on education. Peer group sharing and learning increase knowledge, enhance self-efficacy, and change attitudes for self-management practice [16,17].

#### Diabetes Management in Primary Care Settings in China

Since the 1990s, China has initiated diabetes self-management education programs that have included nurse-based information delivery or clinic counseling targeting inpatients. Literature has shown those programs can improve patients’ knowledge and adherence to medication after intensive short-term interventions [18]. However, the beneficial results could not be sustained in the long term because patients lacked self-efficacy, motivation, and ongoing follow-up support [19,20]. Health policy in China has led to diabetes care and management being delivered mainly in local primary care settings. However, it is difficult to provide personalized health management in rural primary-care settings due to the challenges of professional shortages and limited capacity relative to urban settings [21,22]. Moreover, rural populations often live in worse socioeconomic conditions and have lower health literacy. In rural settings, knowledge, adherence to management practices, and blood sugar control are far from meeting national goals [23,24]. Studies have shown, however, that friends, peers, family members, and community lay health workers may all be important supporters of self-management among individuals with diabetes, especially in areas with restricted health resources [25-27]. Additionally, peer support relies on nonhierarchical, reciprocal relationships, which provide a flexible supplement to formal health system services for people with diabetes. In addition, peer support fosters understanding and trust of health care staff among groups who otherwise may be alienated from or have poor access to health care [28,29]. Peer support implemented through primary care is gaining increased interest in urban China [25,30], while few programs exist in rural areas.

Given the needs in rural areas, and the benefits peer support approaches have achieved in urban settings, this project will explore and assess the feasibility and acceptability of peer support approaches in rural areas. We propose to develop community-based peer support for individuals with type 2 diabetes in rural areas in China. In particular, the study is designed to integrate a peer-support approach into local primary care settings. This study outcome will provide valuable information about the effectiveness, acceptability, and feasibility of a program to improve diabetes self-management in rural, resource-limited communities.

### Study Purposes

Peer support is a culturally adapted, complex intervention; evaluating such an intervention presents challenges to researchers. This study will pursue the following objectives: (1) to evaluate the feasibility and acceptability of a peer support approach to type 2 diabetes self-management in rural primary care settings; (2) to identify enabler and facilitator factors likely to influence the peer support implementation; (3) to provide primary data and evidence for developing a version of the program suitable for a randomized controlled trial in a rural primary care setting.

## Methods

### Overview

This project will include formative evaluation to develop and then implement and evaluate a peer support approach to improve diabetes self-management in rural primary care. Figure 1 shows each phase in the study.

**Figure 1 figure1:**
[figure not shown]
Study phases in detail.

### Study Setting

This study will be conducted in rural communities in Anhui province. Anhui province is located in eastern China and has about 61 million people. It is divided into 3 geographic areas based on the Huai River and Changjiang River. The 3 areas are north of the Huai River, between the Huai River and Changjiang River, and south of the Changjiang River. These 3 different areas have different customs, cultures, and dietary habits. Stratified sampling will identify 1 county in each of the northern, southern, and middle regions. One township will be randomly recruited in each county. Within each township, the village that has the largest number of adults with T2DM will be selected based on the electronic management system of the local primary care system. This will result in 3 villages representing 3 areas in Anhui province with high numbers of adults with T2DM.

### Participant Recruiting

Study participants will be identified through the Community Chronic Disease Management System (CCDMS), which was established as a national primary care package program in communities in both urban and rural areas. Primary care providers (family doctors and public health physicians) in local primary care settings (township hospitals or village clinics) will contact eligible patients to explain the purpose of the study and details of the program. Since this is an exploratory study with a new intervention approach that has never been tested before in rural Anhui Province, no formal calculation of the sample size will be performed. All patients who are registered in the CCDMS in the sampled study setting (villages) and meet the inclusion criteria will be included if they are willing to participate. An estimated 15 to 20 patients will be recruited in each county, yielding a total sample of 45 to 60 participants. Based on the recommendations of Hertzog [31], a sample of 10 to 40 people is sufficient for a pilot study using a single group to estimate the sample size for a future trial.

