#### Phase IV: Peer Supporter–Led Group Meetings and Activities

Participants will be divided into groups with 6 to 10 people and assigned to peer leaders for 3 months based on how close they live to the peer leaders. Groups will be encouraged to take part in biweekly (ie, every second week) group activities with peer supporters. Peer group members will also be encouraged to organize weekly casual activities such as phone calls, WeChat voice messages, physical exercise groups, and group member family visits.

The biweekly meeting content will be based on findings from phase II and adapted and developed together with primary care providers and peer supporters. The peer group sessions will aim to achieve the following key self-management practice objectives: increasing physical activity; promoting healthy eating habits; ceasing tobacco use; reducing alcohol consumption; adhering to medication; engaging in regular clinical care and diabetes management services provided in primary care settings, such as health education classes, blood sugar and blood pressure monitoring, and physical examinations; and coping with negative emotions.

Peer supporters will also be encouraged to contact participants in their groups between the formal group sessions in order to reinforce the program objectives, update on and discuss the content of missed sessions, and encourage goal attainment and attendance at the next peer group session. These contacts may be informal through meetings within their neighborhoods.

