##### Quantitative Evaluation

Key evaluations will be the assessment of differences between baseline and after 3 months (after completion of the peer leader program) in terms of self-management practice, knowledge, self-efficacy, and perception of social support. Additionally, changes will be compared between villages through 2-tailed *t* tests or nonparametric equivalents.

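### The program runs in 6 to 9 peer-leader groups, but the named between-village t tests and the pilot-size claim count independent individuals

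*Protocol article*

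**What the plan says.** Under Phase IV, "Participants will be divided into groups with 6 to 10 people and assigned to peer leaders for 3 months", and the assignment is "based on how close they live to the peer leaders". Study Setting fixes the sites: "This will result in 3 villages representing 3 areas in Anhui province". Participant Recruiting gives the numbers: "An estimated 15 to 20 patients will be recruited in each county", "yielding a total sample of 45 to 60 participants".

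The same section says that "no formal calculation of the sample size will be performed" because the study is exploratory, and then relies on a cited recommendation that "a sample of 10 to 40 people is sufficient for a pilot study using a single group to estimate the sample size" for a later trial.

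For analysis, Quantitative Evaluation lists the baseline-to-3-month differences as the key evaluations without naming a test. It then adds: "Additionally, changes will be compared between villages through 2-tailed" t tests or nonparametric equivalents. Quantitative Data Analyses likewise names tests only for comparing patient characteristics across the 3 settings. Neither the analysis text nor the sample-size text mentions the peer group or the peer leader.

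**The concern.** Members of one group share a leader, a series of meetings and a neighbourhood for 3 months, so their changes in self-care, self-efficacy and perceived support may well be correlated. A two-sample t test on individuals, or its rank-based equivalent, assumes that they are not. With positive correlation the standard error is too small, and a chance difference between groups can pass for a difference between villages.

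The size rationale has a related weakness. Objective 3 is to supply data for a version of the program suited to a randomized trial, and the one statistical justification for the sample is that a single-group pilot of individuals suffices to size that trial. A trial of a group-delivered program needs an ICC and a controlled effect size as well as an SD. A single-arm pilot with fewer than ten groups gives neither in usable form.

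**Working it through.** **The article's own figure.** 3 counties × 15 = 45 and 3 × 20 = 60, so the stated total of 45 to 60 reproduces. The recommendation of 10 to 40 people comes from a cited source, and the article gives no inputs from which to check it.

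**Number of groups.** Assume groups stay within a village, since assignment is by proximity. The possible counts g satisfy 6g ≤ n ≤ 10g. For n = 15 to 17, g = 2; for n = 18 to 20, g = 2 or 3. Over 3 villages that is 6 to 9 groups. If groups could cross villages, the sizes would allow 5 to 10.

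**Design effect.** DE = 1 + (m − 1) × ICC, where m is group size. The ICC of change is an assumption, taken as 0.01, 0.05 and 0.10.

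- m = 6: 1.05, 1.25, 1.50.
- m = 10: 1.09, 1.45, 1.90.
- Naive standard errors are too small by a factor √DE, from √1.05 = 1.02 to √1.90 = 1.38.
- Effective sample at ICC 0.05: 45 people in groups averaging 7.5 give 45/1.325 = 34; 60 people in groups of 10 give 60/1.45 = 41.

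**True error of the named test.** Simulated two-sample t test between two villages with no true village difference, normal changes, correlation at peer-group level only, 100,000 runs per cell, nominal 5%:

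| Layout | ICC 0.01 | ICC 0.05 | ICC 0.10 |
|---|---|---|---|
| N = 45, groups of 8 and 7 per village | 5.8% | 8.9% | 13.0% |
| N = 60, two groups of 10 per village | 6.1% | 10.5% | 16.1% |
| N = 60, groups of 7, 7 and 6 per village | 5.4% | 8.4% | 12.0% |

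At ICC 0 the error is 5.0 to 5.1%, so the excess comes from the grouping. A paired t test on all participants gives nearly the same figures (8.4 to 10.2% at ICC 0.05), but the article does not say that such a test will be used. A t test on group mean changes keeps its error at about 5% in every cell.

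**What the pilot can supply for a future trial.**

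- *SD.* E[s²]/σ² = 1 − (m − 1) × ICC/(N − 1). With N = 45, m = 7.5, ICC 0.05: 1 − 0.325/44 = 0.993. With N = 60, m = 10, ICC 0.10: 1 − 0.9/59 = 0.985. Grouping hardly biases the SD.
- *ICC.* At a true ICC of 0.05, the central 95% of simulated estimates runs from about −0.12 to 0.29 (6 groups, N = 45) or −0.11 to 0.26 (9 groups, N = 60). At m = 7.5 the upper value 0.29 would imply a design effect of 1 + 6.5 × 0.29 = 2.9, and the lower value one below 1. That is no basis for planning.
- *Effect size.* There is no control arm, and the article's limitations section says the before-after comparison may be biased.

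**What a design effect would do later (illustration only).** At an assumed standardized difference of 0.3, two-sided 5% and 80% power, 175 per arm are needed without grouping. With both arms grouped, 175 × 1.05 to 175 × 1.90 gives 184 to 333. With only the intervention arm grouped, 175 × (1 + DE)/2 gives 180 to 254.

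**The case against.** The best defence is that this is an exploratory feasibility study. It states no power, significance threshold or formal sample size, and the move to a trial depends on feasibility and acceptability, judged largely from qualitative work. The lack of a control group is disclosed. The ICC is unknown, and at 0.01 the standard errors are off by only about 2 to 4%. All of this stands, and it limits the weight of the point.

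A reader might infer three stronger conclusions that the article does not support.

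- *That the pre-post intervals will be too narrow.* No test, model or interval is named for that comparison, and a fuller plan may handle grouping properly. The stated problem lies in the between-village tests.
- *That the future trial will be undersized.* The article gives neither its unit of randomization nor its sizing method, and the pilot SD is nearly unbiased. Undersizing would follow only if the design effect were left out or the uncontrolled change were used as the effect size.
- *That 45 to 60 participants are too few.* For feasibility aims they are not, and nothing here calls for more.

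It is also fair to object that asking this pilot to estimate the ICC would be no remedy, given the range shown above.

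The defence leaves two positive statements standing: a named individual-level test of change between villages, and a claim that a count of individuals in one group suffices to size a later trial. Both sit badly with delivery through peer groups.

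**Conclusion.** The point holds in a limited form. The between-village t tests are too liberal if the ICC of change within peer groups is positive: modestly at 0.01, and roughly two to three times the nominal 5% at 0.05 to 0.10. The claim that the pilot suffices to size a future trial goes further than the design allows: it can give an SD, but not a usable ICC or a controlled effect size.

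This rests on groups staying within villages, on an ICC range that is assumed and not taken from the article, and on no further correlation at village level. The point is worth acting on because the correction is cheap, not because it threatens the feasibility aims.

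**What to change.** - *Pre-post change.* Report it with intervals that allow for peer group. A simple choice is the mean change per group, with a t interval on groups minus 1 degrees of freedom (5 to 8).
- *Between villages.* Present changes by village descriptively, without p values, since each village has only 2 or 3 groups.
- *Participant Recruiting.* Replace the sufficiency claim with wording such as: the pilot will supply feasibility rates and an SD; it will not supply a usable ICC or a controlled effect size; the future trial's sample size will apply a design effect over a stated range of ICCs from external sources and will not take its effect size from the uncontrolled pre-post change.

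No extra participants or data are needed beyond recording each participant's group. The cost is wider intervals: through the critical value alone, 2.57/2.01 = 1.28 times as wide with 6 groups (5 against 44 degrees of freedom) and 2.31/2.00 = 1.15 times with 9 groups (8 against 59), even if the ICC is zero. The stated purpose of the sample also becomes narrower.
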